## Abstract

**Background:**

Early childhood is a crucial time to foster healthy eating and physical activity (PA) habits, which are critical for optimal child health, growth and development. Child care facilities are important settings to promote healthy eating and PA and prevent childhood obesity; however, almost all prior intervention studies have focused on child care centers and not family child care homes (FCCH), which care for over 1.6 million U.S. children.

**Methods:**

This paper describes Healthy Start/Comienzos Sanos, a cluster-randomized trial evaluating the efficacy of a multicomponent intervention to improve nutrition and PA environments in English and Spanish-speaking FCCH. Eligible child care providers complete baseline surveys and receive a two-day FCCH observation of the home environment and provider practices. Parent-consented 2–5 year-old children are measured (height, weight, waist circumference), wear accelerometers and have their dietary intake observed during child care using validated protocols. FCCH providers are then randomly assigned to receive an 8-month intervention including written materials tailored to the FCCH providers’ need and interest, videos, peer support coaching using brief motivational interviewing, and periodic group meetings focused on either nutrition and PA (Intervention) or reading readiness (Comparison). Intervention materials focus on evidence-based nutrition and physical activity best practices. The initial measures (surveys, two-day observation of the FCCH and provider practices, child diet observation, physical measures, and accelerometer) are assessed again 8 and 12 months after the intervention starts. Primary outcomes are children’s diet quality (Healthy Eating Index), time in moderate and vigorous PA and sedentary PA during child care. Secondary outcomes include FCCH provider practices and foods served, and PA environments and practices. Possible mediators (provider attitudes, self-efficacy, barriers and facilitators) are also being explored. Process evaluation measures to assess reach, fidelity and dose, and their relationship with dietary and PA outcomes are included.

**Discussion:**

Healthy Start/Comienzos Sanos fills an important gap in the field of childhood obesity prevention by rigorously evaluating an innovative multicomponent intervention to improve the nutrition and physical activity environments of FCCH.

**Trial registration:**

(# NCT02452645) ClinicalTrials.gov Trial registered on May 22, 2015.

**Electronic supplementary material:**

The online version of this article (10.1186/s12889-019-6704-6) contains supplementary material, which is available to authorized users.

## Background

Obesity among U.S. preschool aged children (2–5 years) has nearly tripled over the last 30 years [1–6], which is of concern, given that children who are overweight by age 5 are more susceptible to obesity later in life [7], leading to serious health problems [8, 9]. An alarming 22.8% of preschoolers are overweight or obese [5], with low-income and ethnic/racial minority children disproportionately affected [3–5, 10]. Healthy eating and physical activity during early childhood are critical for optimal health, growth and development [11, 12], and poor diets and lack of physical activity increase children’s risk for obesity and related health problems [13–44]. Unfortunately, diet and physical activity patterns of preschoolers, especially low-income and racial/ethnic minorities, often do not meet national guidelines [26, 45]. Effective interventions are needed to improve preschoolers’ food and physical activity environments and behaviors to prevent the development of obesity and related conditions.

Child care settings provide a valuable opportunity to promote healthy eating and physical activity. More than 70% of preschoolers with working mothers are enrolled in out-of-home child care, spend up to 40 h there a week, and consume most of their daily calories while in care [4, 46–49]. Thus, interventions to improve the nutrition and physical activity environments in child care settings are greatly needed [12, 50–54], especially among providers who serve low income, ethnically diverse families.

Among the few reported interventions conducted in child care settings, most have been effective at improving children’s dietary, physical activity and screen-time behaviors [47]; however, all of these studies were conducted in child care centers and none in family child care homes (FCCHs), which care for 25% of US preschoolers [55]. FCCHs have different standards and environments than child care centers, and may not routinely meet best practice guidelines for nutrition or physical activity [31, 56]. Also, children enrolled in FCCHs may be at increased risk for obesity compared to children in center-based care [46]. Thus, obesity prevention interventions in FCCH are critically needed, especially in homes that care for higher risk children. While one randomized obesity prevention intervention trial in FCCH is underway in North Carolina [57, 58], results have not yet been reported, and no studies have included Spanish-speaking family child care providers (FCCP).

This paper describes the interventions, study protocols and measures used in the ‘Healthy Start/Comienzos Sanos’ study (hereafter called Healthy Start). Healthy Start is an innovative multicomponent intervention that engages English and Spanish-speaking FCCPs to improve their food and physical activity-related practices, the nutrition and activity environment of the FCCH, and improves the diet, physical activity and screen-time behaviors of the 2-to-5 year-old children in their care. We hypothesize that FCCP receiving the Healthy Start intervention will have greater changes in nutrition and physical activity practices and environments compared with those in the control group, which received intervention on reading readiness, but no content on nutrition and physical activity.

## Methods

### Study overview, aims and hypotheses

Healthy Start is an ongoing cluster randomized trial with plans to recruit 132 family child care providers (FCCPs) who care for 2–5-year old children. The Specific Aims of the study are to conduct: 1. Formative research to inform the development and adaptation of the FCCH intervention; 2. A cluster-randomized trial to evaluate the efficacy of the nutrition and physical activity intervention among 66 FCCP who receive the Healthy Start intervention and 66 demographically-matched FCCPs who receive a comparison intervention). Primary outcomes include children’s dietary quality, physical activity and sedentary behaviors screen-time at FCCHs. Secondary outcomes include the food, physical activity and screen-time environments of FCCHs and the food and activity-related practices of FCCP. Also to be explored are the relationships between outcome measures and the intervention dose received by the FCCP; the relationship between outcome measures and potential mediating and moderating variables; and the intervention’s effect on the body mass index (BMI) of 2-to-5 year-old children in FCCHs.

Evaluations before and after the intervention include phone and in-person surveys with the FCCP, two-day observations of the FCCH and children’s dietary intake as well as accelerometer and anthropometric measurements of children. After the baseline assessment, FCCH are randomized in matched pairs into either the nutrition and physical activity Intervention group or a Comparison group that receives literacy and reading readiness intervention. The Institutional Review Boards of Brown University, University of Rhode Island and University of Connecticut approved all study procedures and materials. A community advisory board is guiding the study.

### Formative research

To inform the development of the intervention and evaluation protocols, researchers conducted focus groups with FCCPs in Rhode Island. The initial four focus groups included 31 FCCPs; all participants were Hispanic and Spanish speaking; most not born in the US (97%) and nearly half (46%) had a high school degree or less [59]. Providers discussed their perceptions and beliefs regarding what influences physical activity, screen time, and dietary behaviors of the children in their care. They also discussed their own nutrition, physical activity, and screen time practices while caring for children and barriers to meeting best practice guidelines.

FCCPs reported feeling responsible for the health of the children in their care. Although they were aware of the importance of healthy eating and physical activity, implementing these practices was sometimes challenging. These barriers included: costs of providing healthier meals, limited space in FCCHs to encourage more physical activity, finding age-appropriate activities for the wide age range of children in their care, and inappropriate parental beliefs around nutrition and physical activity. Providers agreed that having more resources, activity ideas, and trainings around nutrition, screen-time and physical activity would be helpful to support a healthier FCCH environment. The importance of communicating with parents about healthy eating and physical activity in the FCCH was also considered important [59].

An additional three Spanish-speaking focus groups (*n* = 15) were held later in Rhode Island (RI) with Hispanic FCCPs and one focus group was held in English (*n* = 5). Among these four focus groups two-thirds spoke Spanish only, and 43% had a high school degree or less. Findings were similar to the first four focus groups conducted. The main difference found was that English-speaking providers did not feel that it was their place to change parents’ nutrition and activity-related behaviors and that the child’s home is separate from the child care environment. In contrast, Spanish speaking providers felt like they could play a role in helping to improve parent’s behaviors and the child’s home environment. In addition, there were differences between the Spanish and English-speaking FCCPs in the foods that they reported serving. English-speaking providers reported that they were more reluctant to use spices because the children may not like them and they were more likely to serve “kid foods” like chicken nuggets and hot dogs than Spanish speaking providers who often served Hispanic meals like rice and beans. English speaking FCCPs tended to live in areas with more indoor and outdoor play space and more outdoor play equipment. Thus, playing outside appeared to be a more regular practice in English-speaking than Spanish-speaking FCCH, with the latter discussing the barriers of living on the second or third floor and needing to walk to a park. Also, English-speaking providers were more likely to discuss searching and using internet-based resources such as YouTube videos of dancing and songs for preschoolers. The findings from all 7 focus groups informed the development of the nutrition and physical activity intervention to address attitudes, beliefs and barriers expressed by the FCCPs and also informed the development of the evaluation measures.

Prior to the start of the study, cognitive assessment testing was conducted with all evaluation surveys to assess comprehension, terminology and culturally appropriateness. Six FCCPs from RI were recruited to undergo individual cognitive assessment testing with a bilingual study staff member. The phone baseline survey and in-person baseline survey were each tested individually with two Spanish speaking FCCPs and one English speaking FCCP. Staff members read questions in multiple formats, or asked questions to clarify participants’ understanding of specific word choices in the questions or responses. Participants were also encouraged to ask for clarification of any questions that were unclear. The staff member also asked the participant to explain her reasoning for the response choice she made. The information collected in these sessions was used to inform final revisions to the baseline evaluation measures prior to their use with study participants.

### Recruitment

#### Provider recruitment

The following strategies are being used to recruit FCCPs for the study: 1. Information sessions by research staff members held at community organizations that provide training and support for FCCPs. These organizations also offer recruitment flyers and brochures to FCCPs who come into their offices; 2. Meetings with the coordinators of FCCP systems who then email study information to FCCPs in their systems; 3. Recruitment sessions at conferences organized for FCCPs; 4. Direct mailings followed by staff phone calls to licensed FCCPs whose contact information was available in state databases in Rhode Island (RI), Connecticut (CT) and Massachusetts (MA); 5. Word of mouth referrals from FCCPs already participating in the study. Interested FCCPs are then contacted by research staff to complete a telephone eligibility survey.

#### Provider eligibility criteria

To be eligible for the study, participants must be a FCCP within 60 miles of Providence, RI, have been operating a FCCH for at least 6 months with plans to remain in operation for at least 1 year; read and speak Spanish or English; have a working phone; have at least one 2–5-year-old child in their care for at least 10 h per week, and who eats at least one meal and one snack prepared by the FCCP during their time at the FCCH. In addition, FCCPs cannot plan to close their FCCH for more than 3 consecutive weeks during the year following their enrollment in the study.

### Outcome evaluation protocols and measures

#### Evaluation overview and randomization procedures

Evaluation measures are conducted with each FCCP at baseline, with the same measures administered when the 8-month intervention is completed and again after 4 months (approximately 12 months after the intervention begins). At baseline, eligible FCCPs complete the first part of the baseline survey on the telephone. Upon completion of this survey, time is scheduled for the project field coordinator to conduct an in-person visit at the FCCH. During this visit, the field coordinator completes the enrollment process, which includes review of the study protocols and expectations, completion of the informed consent and implementation of the second part of the baseline survey. The field coordinator also leaves written consent forms for the parents of the age-eligible children in the FCCH. For a child to participate in the evaluation, parents must give consent for their child to have diet observed by project staff, wear an activity monitor and/or undergo anthropometric measurement. When at least one signed parent consent form is obtained giving permission for at least one of the measures, the two-day observation is scheduled with the FCCH.

The two-day observation by research staff members includes measurement of the physical and social environment of the FCCH as well as children’s dietary intake. During these visits, staff members also conduct anthropometric measures of the eligible children whose parents consented. Consented children also wear accelerometers during the 2 days to measure their activity. Evaluation staff are blinded to group assignment to reduce measurement bias. All measures are described in detail below.

Once FCCPs complete the entire baseline survey and in-home observation, they are randomized into either the Intervention or Comparison group. FCCPs are randomized in pairs matched based on their primary language spoken and the number of eligible children within the age range of 2–5 years in their FCCH. The data manager randomly assigns all participants to experimental groups using a Microsoft Excel randomization function after which participating providers are notified of their assignment by a phone call from the project coordinator. Evaluation staff members are not made aware of the intervention group assignment during any aspect of data collection preparation or conduct in the field. Participation in the Healthy Start study, and all data collected through observation or other means are stored in a secure, password protected network or in locked file cabinets.

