#### Exploration of group assignment

Demographic and other baseline characteristics will be compared between groups to confirm that the random assignment resulted in statistically similar groups. Any variables found to be different between groups at baseline will be included in final models. Child-level outcomes will be adjusted for clustering at the FCCH level using generalized estimating equation (GEE) models with exchangeable correlation matrices.

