#### Analysis plan

Initially, descriptive statistics will be used to summarize the variable and detect outliers, data entry mistakes and missing values, including exploratory graphical techniques. The normality of the distribution of primary and secondary outcomes, both in their original and transformed state (if necessary), will be examined with a normal probability plot. Demographic and other baseline characteristics will be compared between groups to confirm that the random assignment resulted in statistically similar groups. Any variables found to be different at baseline will be included in adjusted models. Child-level outcomes will adjust for clustering at the FCCH level using GEE models with exchangeable correlation matrices. We will explore the assessment of the intervention’s effectiveness at changing the HEI, physical activity, sedentary behavior variables, and exploratory measures of BMI and BMI z score by experimental group using Analysis of Co-Variance (ANCOVA).

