#### Potential mediators and moderators

Potential mediators include FCCP attitudes, beliefs, perceived barriers and self-efficacy measured on the pre-post surveys. Potential moderators include provider age, ethnicity, race, educational level, income level, years in operation as a FCCP, size of FCCH (number of children in care), accept CACFP or not, and hours of training in the past year.

We will explore the mediational hypothesis, which assumes that interventions change mediators, which in turn change outcome behaviors. We will first assess the experimental group variable (Intervention or Comparison) with the primary outcome behaviors. We will then link the experimental group variable with changes in the proposed mediator (e.g., FCCP’s self-efficacy) and will link proposed mediator with the behavioral outcome. We will repeat these steps looking at all potential mediation relationships hypothesized in the intervention logic model. Clearly, the proposed sample size does not provide sufficient power to test simultaneously all these possible mediators without the risk of capitalizing on chance. However, the information gathered from the individual mediational analyses will provide important preliminary data for generating new hypotheses regarding the intervention’s impacts within FCCH and will guide future intervention research.

For moderation, the GEE models described above will be elaborated by including main effects and interactions with experimental condition of putative moderators of the treatment effect, i.e., provider demographic variables. The additional model terms will allow us to test whether these moderating variables were related to changes in outcomes from baseline to 8 or 12 months, and, further, whether these effects differed by treatment.

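### Homes are randomised in pairs matched on language and number of eligible children, but the stated models do not carry these factors, so the test is somewhat conservative if they predict the outcome

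*Protocol article*

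**What the plan says.** Two places in the protocol article fix the randomisation. Under Study overview, aims and hypotheses: "FCCH are randomized in matched pairs into either the nutrition and physical activity Intervention group or a Comparison group". Under Evaluation overview and randomization procedures, the matching factors are named: "FCCPs are randomized in pairs matched based on their primary language spoken and the number of eligible children" in the 2 to 5 age range.

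The analysis is set out under Exploration of group assignment and Analysis plan. For clustering: "Child-level outcomes will adjust for clustering at the FCCH level using GEE models with exchangeable correlation matrices". The intervention effect on diet quality, activity and sedentary behaviour is assessed "by experimental group using Analysis of Co-Variance (ANCOVA").

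The covariate rule appears twice. Under Exploration of group assignment: "Any variables found to be different between groups at baseline will be included in final models". Under Analysis plan: "Any variables found to be different at baseline will be included in adjusted models". Neither section mentions the pair, provider language or the number of eligible children. The nearest variable in any model is "size of FCCH (number of children in care"), which is total enrolment. It appears only as a potential moderator in exploratory interaction models.

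**The concern.** The design treats language and number of eligible children as important enough to restrict the randomisation, but the stated analysis treats the arms as two independent samples of homes. The covariate rule works against the design. It is triggered by a difference between arms, and matching removes that difference for exactly these two variables.

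If matched homes resemble each other on the outcome, the true variance of the treatment contrast is smaller than an unpaired model estimates. The reported standard error is then too large, the confidence interval too wide and the test conservative. Part of what the matching could buy is not collected.

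The article gives some reason to expect such a resemblance. Its Formative research section reports that Spanish- and English-speaking providers differed in the foods they served and in how regularly children played outdoors. Both bear on the primary outcomes.

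**Working it through.** **The plan's own figure.** Sample size considerations gives 60 homes per group with 3 children each, power of at least 0.8 and alpha .05. This cannot be reproduced, because no SD, intracluster correlation or within-pair correlation is stated. Taking alpha as two-sided (assumed), 60 homes per arm at 80% power corresponds to a difference of (1.960 + 0.842) × √(2/60) = 0.511 SD of home means. That effect is used below.

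**Set-up.** Let r be the correlation between the two home means in a pair, given arm. It is not in the documents, so a range of 0 to 0.3 is assumed. With n pairs, the true variance of the difference in means is 2σ²(1 − r)/n. An unpaired model estimates 2σ²/n. Hence:

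- SE ratio (nominal/true) = 1/√(1 − r)
- Actual alpha = 2Φ(−1.960/√(1 − r))
- Power, matching ignored = Φ(0.842/√(1 − r))
- Power, matching used = Φ(2.802/√(1 − r) − 1.960)

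Example, r = 0.2: 1/√0.8 = 1.118. Alpha = 2Φ(−2.191) = 0.028. Power ignoring the matching = Φ(0.941) = 82.7%. Power using it = Φ(1.172) = 87.9%.

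| r | SE ratio | Actual alpha | Power, ignored | Power, used | Loss (points) |
|---|---|---|---|---|---|
| 0 | 1.000 | 5.0% | 80.0% | 80.0% | 0 |
| 0.05 | 1.026 | 4.4% | 80.6% | 82.0% | 1.4 |
| 0.10 | 1.054 | 3.9% | 81.3% | 84.0% | 2.7 |
| 0.20 | 1.118 | 2.8% | 82.7% | 87.9% | 5.3 |
| 0.30 | 1.195 | 1.9% | 84.3% | 91.8% | 7.5 |

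Power with the matching ignored also rises with r. The estimator's true variance falls under matching whether or not the model uses it.

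**Does the covariate rule pick up the factors?** A home-level simulation used 66 pairs matched on a binary language variable and a count of children, 10% attrition and 4,000 runs per setting. A baseline test at the 5% level selected a matching factor in 0% of runs. With the two factors explaining 20% of home-level variance, type I error was 0.033 unadjusted and 0.051 adjusted for them. Power was 81% unadjusted and 87% adjusted.

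**If the ANCOVA includes the baseline outcome.** The article does not name the ANCOVA covariate, so this is an assumption. Let the factors explain a share R of home-level variance equally at both visits, and let the remainder correlate ρ between visits. The SE without the factors, divided by the SE with them, is √{[1 − (R + ρ(1 − R))²] / [(1 − R)(1 − ρ²)]}. For R = 0.2 and ρ = 0.5 this is √(0.64/0.60) = 1.033. For R = 0.1 / 0.2 / 0.3 the excess is:

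- ρ = 0.3: 2.7 / 5.2 / 7.8%
- ρ = 0.5: 1.7 / 3.3 / 4.9%
- ρ = 0.7: 0.9 / 1.7 / 2.6%

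**Cost of the adjustment if the factors predict nothing (r = 0), t-based.** Power is 79.4% unadjusted (118 df), 79.3% with the two factors (115 df) and 78.7% with a term for each pair (59 df).

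**The case against.** The strongest reply is that the stated analysis is valid. It has no bias, and its type I error is at or below 5%. The loss exists only relative to a better analysis. All of that stands.

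The size is also uncertain. The evidence that language is prognostic comes from focus groups, with one English-language group of 5 providers, and nothing comparable is reported for the number of eligible children. It describes differences in level, whereas the primary outcomes are changes. A baseline-outcome covariate or change scores would absorb much of a stable level difference. This stands too and is why the range above includes zero.

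A reader might infer that the covariate rule forbids the matching factors. It does not. It says which variables will enter, not that no others may. The exclusion is one of effect, and loose matching could leave a difference that lets a factor in.

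Finally, a full covariate list is commonly left to the SAP, which is not shown. That would answer mere silence. Here the article states both the models and a selection rule, and that rule is poorly suited to a matched design, so the point survives.

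**Conclusion.** The point holds as an efficiency matter. The stated analysis does not follow the randomisation, and its covariate rule will in practice not repair this. For an assumed within-pair correlation of 0 to 0.3, the standard error is overstated by 0 to 20% and 0 to about 7.5 points of power are forgone. The lower end is more likely if the ANCOVA adjusts for the baseline outcome. These figures rest on home means as the unit, normal approximations and a correlation the documents do not give.

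Three stronger readings are not supported:

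- **The trial is underpowered because of this, or its test is invalid.** Power stays at or above the unmatched figure at every r, and the error is conservative.
- **Power rises from 80% to 84 / 88 / 92%.** At the same effect, the analysis ignoring pairs already has 81 / 83 / 84%.
- **Primary language must join the moderators.** That list opens with "Potential moderators include provider age, ethnicity, race, educational level, income level", is exploratory and is not worded as closed. Adding language is a separate preference with no bearing on the standard error.

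The weight is minor to moderate: worth changing because it costs almost nothing, not a condition for the trial's validity.

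**What to change.** In Exploration of group assignment and in Analysis plan, add a sentence along these lines: *Provider primary language and the number of eligible 2–5-year-olds in the home at randomisation, the factors used for matching, are included as covariates in every primary outcome model, whatever the baseline comparison shows.*

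Both variables are known before randomisation because they define the pairs, so no new data are needed. The cost is 2 or 3 degrees of freedom out of about 120 homes, or about 0.1 point of power if the factors predict nothing. Covariates are preferable to a term for each pair, which would use about 59 degrees of freedom and lose a pair's information when one of its homes drops out. The sample size need not change.
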